### Eligibility criteria

#### Inclusion criteria

To be included the PSV must be a licensed operator and must have valid motor vehicle insurance.

#### Exclusion criteria

PSVs will not be included in the study if they do not have valid motor vehicle insurance; and do not have a license to operate as a PSV.

### Study outcomes (Table 2)

ᅟ

**Table 2 Tab2:** Study Outcomes

No.	Study Comparison	Variable	Indicator	Source
1. Primary Outcome Indicator				
1	Difference between intervention and control buses	Change in traffic crash rate per 1000 buses over a 14-month period	Whether the bus experienced a road traffic crash as reported from motor vehicle insurance claims among those buses during 7-month period of study or 7-months prior to study	Data on motor vehicle insurance claims
2. Secondary Outcome Indicators				
2	Difference between intervention and control buses	Change in the traffic crash rate per 1000 buses overtime for a 14-month period (monthly analysis)	Whether the bus experienced a road traffic crash as reported from motor vehicle insurance claims for each month for the 7-month period of study or 7-months prior to study (repeated measures or monthly analysis)	Data on motor vehicle insurance claims
3	Difference between intervention and control buses	Change in crashes resulting in fatalities per 1000 buses over a 14-month period	Total number of fatalities from road traffic crashes during the period of the study as compared to the 7 months prior to the study	Data on motor vehicle insurance claims
4	Pre vs. Post (overall and not separated per arm)	Mean number of road traffic crashes	Total number of road traffic crashes during the period of the study as compared to the 7 months prior to the study	RTSA data and Zambia road traffic police reports;

Lists one primary outcome of interest and three secondary outcomes of interest. The primary source of information will be data from motor vehicle insurance claims while road traffic police reports will be used for only one secondary outcome

### Study outline (Fig. 4)

ᅟ

**Fig. 4 Fig4:**
[figure not shown]
Study outline. The monitoring of the intervention will be done by RTSA as part of their already existing routine inspection exercises of PSVs

### Data collection procedures

#### Motor vehicle insurance claims data

Data on all the claims made during the intervention period will be collected from the general insurance companies where PSVs enrolled in the study have their insurance. The main variables to be reported include date of loss; registration number; location of accident; and classification of accident and severity of accident. An accident will be defined as any collision with another vehicle, pedestrian, animal, or any stationary object such as a tree, pole or building. A claim for the incident does not have to be made with the insurance company for it to qualify as an accident.

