### Intervention: New RTSA road safety bus sticker

For the intervention arm of the study, RTSA will be responsible for distribution of the stickers as well as routine inspection of the vehicles to ensure that road safety bus stickers are continuously displayed throughout the evaluation. The stickers will be placed within minibuses and long distance big buses (seating capacity of at least 54 passengers).

In the minibuses, these stickers will be placed on the panels between the passenger window and the ceiling of the vehicle. Approximately six stickers will be placed in each minibus ensuring that at least one sticker is within eye view of each passenger in the vehicle. In the big buses, between 10 and 16 stickers will be placed in each and the placement will vary depending on the design and size of the bus. They could be placed on panels between the passenger window and the ceiling of the vehicle, behind the driver’s seat, or overhead above the televisions, as long as at least one is within eye view of each passenger.

Big buses are routinely inspected before they leave the central bus stations for their long distance journeys. Minibuses will be inspected during routine RTSA road checks, within bus stations and during regular RTSA vehicle inspections. The road safety bus stickers’ campaign and monitoring of minibuses and big buses will occur for approximately 7 months.

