### Sample size and selection

For a conservative measure of effect, and thus a more conservative and larger sample size, we propose a difference-in-difference primary analysis examining data from 7 months before compared to the 7 months after the implementation of the intervention (and not disaggregated into monthly measures). Based on budget constraints and logistics, we estimated the minimal person time for minibuses assuming we would like to see a minimal effect of 0.01 absolute difference in the *change* in the accident rate per 1000 minibuses over the 14-month period (7-month pre vs. 7-month post). This change is similar to that of the Kenya study. Table 1 presents the inputs used for this equation, assuming the accident rate reported within the Kenya study among the controls would be generalizable to Zambia [20]. To account for potential spillover due to the fact that passengers will transfer between buses (though we assume drivers to remain within the same buses), we assumed that the control arm would have slight improvement in the accident rate over the 14-months observed. Additionally, the equation assumes an alpha of 0.05 and power (beta) of 80%. The equation used is as follows [22]:$$ N\  person- years\ in\ each\  arm={\left({Z}_{\frac{\alpha }{2}}+{Z}_{\beta}\right)}^2\Big[\left({\lambda}_0+{\lambda}_1\right)/{\left({\lambda}_0-{\lambda}_1\right)}^2 $$

**Table 1 Tab1:** Sample size calculation parameters

Z_a/2_	Type I error	1.96
Z_B_	Type II error	0.84
*λ* _0_	Estimated change in the accident rate per 1000 minibuses over the 14-month period in the control arm	−0.01
	Absolute difference	.01
*λ* _1_	Estimated change in the accident rate per 1000 minibuses over the 14-month period in the intervention arm	−0.02
y	Number of person years in each arm	116
	Number of cars assuming cars followed for 1.16 years or 14 months	954
	Number of vehicles to follow with 10% buffer per arm	1060

The sample size calculation formula in Table 1 used is adopted from Hayes & Mouton (2009). A buffer of 10% was included to allow for buses that may drop out of the study during recruitment for any reason

For the big buses, there is a finite sample of buses and we intend to enroll all big buses from within the sampled areas.

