### Data analysis

At endline, full analysis will be performed using data from the full 14-month period. To assure balance between the study arms, we will compare characteristics between our two arms including insurance company provider and accident rates in the past year. Additionally, utilizing the insurance claims data, we will compare the insurance claim rate per 1000 vehicles in the 7 month period before the intervention.

For the primary outcome of the study in which will examine the change in the road traffic accident rate over the 14-month period for the intervention arm compared to the change in the road traffic accident rate over the 14-month period for the control arm, we will use a difference-in-difference analysis. To this end, we will run a difference-in-difference analysis that will be comparing the intervention and control groups using regression analysis of the following format, and adjusting the SE to account repeated measures (i.e. cluster) from the bus:$$ {\mathrm{Y}}_{\mathrm{rate}}={\upbeta}_0+{\upbeta}_{\mathrm{Sticker}}{\mathrm{X}}_1+{\upbeta}_{\mathrm{Post}}{\mathrm{X}}_2+{\upbeta}_{\mathrm{Sticker}\mathrm{Post}}{\mathrm{X}}_3+\mathrm{e} $$

For the primary outcome regression, Y is the occurrence of a road traffic crash (indicator 1, 0); X_1_ is the indicator for whether or not the bus was in the intervention arm or control arm (i.e. 0, 1); X_2_ is the indicator for the time period with a value of one indicating the seven-month post intervention period; X_3_ being the interaction indicator between the presence of the new RTSA road safety sticker and the post intervention period (difference-in-difference impact estimate). Additionally in this regression above, the β_Sticker_ estimate will provide the relative difference in the accident rate between intervention and control arm during the pre-intervention period; β_Post_ will be provide the relative change in the accident rate in the control group from pre- to post- intervention period; and, β_StickerPost_ will be the relative difference between the control and intervention group in the change in the outcome from pre to post intervention (i.e. our main estimate of effect). We will appropriately adjust for baseline imbalance between the two arms including insurance provider. To assure outcomes are more meaningful, the rates and thus betas for outcome 1 and 2 will be transformed to report per 1000 minibuses. This regression will then be replicated for the remaining study outcomes.

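### The insurer data-collection paragraph covers only claims made in the intervention period and counts crashes without a claim, which conflicts with a primary outcome built on claims from both 7-month windows

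*Protocol article*

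**What the plan says.** The protocol article describes the insurer data in one place, the subsection on motor vehicle insurance claims data under Data collection procedures, which reads: "Data on all the claims made during the intervention period will be collected from the general insurance companies". The intervention section gives the length of that period: the campaign and "monitoring of minibuses and big buses will occur for approximately 7 months". The data-collection paragraph lists date of loss among the variables to be obtained. It then defines an accident as a collision and adds: "A claim for the incident does not have to be made with the insurance company for it to qualify as an accident".

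Other sections set different requirements.

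- Sample size and selection describes the primary analysis as "examining data from 7 months before compared to the 7 months after the implementation of the intervention".
- Table 2 defines the primary indicator as a crash "as reported from motor vehicle insurance claims among those buses during 7-month period of study or 7-months prior to study". It names insurance claims as the source for outcomes 1, 2 and 3, and its note says that "road traffic police reports will be used for only one secondary outcome".
- Data analysis plans to use the whole 14 months and, from the claims data, states that "we will compare the insurance claim rate per 1000 vehicles in the 7 month period before the intervention".
- The Discussion accepts that some crashes never lead to a claim and treats this as measurement error in the outcome.

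**The concern.** The paragraph that an insurer's data request would naturally follow disagrees with the outcome table and the analysis section on two matters: which months of claims are needed, and whether an event needs a claim at all.

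The first bears on whether the primary effect can be estimated. The main estimate is the interaction of arm and period, so it needs observations in both periods. The second bears on what is counted. A definition that admits unclaimed crashes cannot be applied from a claims file, and no other source is named for outcomes 1 to 3.

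A smaller matter follows from the wording. If records are selected because the claim was made within the window, a crash late in the post period whose claim arrives after the window closes is never extracted.

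**Working it through.** **Window.** The regression in Data analysis has an intercept, X1 (arm), X2 (1 in the post period) and X3 (the interaction, X1 × X2).

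- Suppose only intervention-period observations are held. Then X2 = 1 on every row.
- X2 is then identical to the intercept column, and X3 = X1 × 1 = X1.
- Four coefficients rest on two distinct columns, so β_Post and β_StickerPost cannot be estimated. Only the post-period difference between arms (β_Sticker + β_StickerPost) is identified, and that is not the stated primary analysis.
- If the extract is dated by loss, a few pre-period losses that were filed late would appear in it. They would be a selected fraction of pre-period crashes and could not serve as a baseline rate.

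The planned pre-period balance check and the pre-period parts of outcomes 2 and 3 would lack data in the same way.

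**Event definition.** Three statements stand side by side.

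- Data collection: a crash counts whether or not a claim is made.
- Table 2: outcomes 1 to 3 are taken from claims data, and police reports serve one secondary outcome only (outcome 4).
- Discussion: crashes without a claim are missed.

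The second and third agree with each other. The first agrees with neither.

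**Late-filed claims.** The documents give no filing lag, so an assumption is needed. Take losses spread evenly over 7 months and a mean lag of m months between loss and claim. The share of post-period losses filed after the window closes is about f = m / 7. This is slightly too high if some lags exceed 7 months.

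| Assumed mean lag m | f = m / 7 |
|---|---|
| 0.5 months | 0.5 / 7 = 7% |
| 2 months | 2 / 7 = 29% |

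Now suppose baseline claims are complete, the arms have equal baseline rates and the lag is the same in both arms. For rare events, the difference-in-difference on the absolute scale becomes (1 − f) × (true post-period difference). Applied to the absolute difference of 0.01 in Table 1:

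- m = 0.5: 0.01 × (1 − 0.07) = 0.0093
- m = 2: 0.01 × (1 − 0.29) = 0.0071

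The ratio of post-period rates between arms is unchanged, because (1 − f) cancels. The plan, however, reports its estimates per 1000 buses, which is an absolute scale. The lost claims would also fall in the last months of follow-up, which the monthly analysis (outcome 2) relies on to see whether the effect fades.

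**The case against.** The best defence is that the paragraph is loosely worded and nobody would act on it. It never says that collection is restricted to the intervention period. The sample-size section, Table 2 and the analysis section all require the earlier 7 months, and the analysis section says that pre-intervention claim rates will be compared. That defence stands as far as intent goes. A reader might infer that the trial was designed without baseline claims, and the documents do not support that.

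A reader might also infer that crashes will be assigned to periods by filing date, so that pre-period crashes filed after the stickers went up count as post-period events. This too is unsupported. No section states such a rule, date of loss is a listed variable, no filing date is listed, and Table 2 asks whether the bus experienced a crash in the period. The 7% to 29% therefore measures possible loss of late-filed post-period claims. It does not measure misassignment between periods.

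On the event definition, the no-claim sentence may be a general definition that also serves outcome 4, or it may refer to incidents notified to an insurer without a formal claim. Either is possible, but the text says neither. The documents show no route by which unclaimed crashes would enter outcome 1, so unequal ascertainment between arms or periods is not demonstrated.

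Finally, a run-off rule is a detail that an article may leave to the full protocol, and nothing suggests that filing lag differs between odd and even plates. Both points are fair. But the selection rule is stated here, and as stated it loses late claims. An equal lag protects the ratio between arms and not the absolute contrast.

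**Conclusion.** The point holds as an internal inconsistency in the data-collection paragraph. On the window, the paragraph conflicts with the sample-size section, Table 2 and the analysis section. This is probably a drafting error, but a request written from it would leave the main difference-in-difference term inestimable. On the event, it conflicts with Table 2 and the Discussion.

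The loss of late-filed post-period claims is a further consequence of the wording, and its size is unknown. The range of roughly 7% to 29% rests wholly on an assumed mean lag of 0.5 to 2 months and evenly spread losses. The matching shrinkage of the absolute contrast also assumes complete baseline claims, equal baseline rates and an equal lag in both arms.

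**What to change.** Amend the paragraph on motor vehicle insurance claims data in three respects.

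1. Request every claim on enrolled buses, in both arms, with a date of loss in the full 14-month window (7 months before and 7 after). Extract after a short run-off whose length is stated in advance.
2. Define the event for outcomes 1 to 3 as a collision with an insurance claim, placed in its period by date of loss.
3. Delete the sentence that waives the need for a claim, or restrict it to outcome 4.

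The cost is a change of wording in the insurer request and a delay in extraction equal to the run-off. The measurement error from unclaimed crashes remains, as the Discussion already acknowledges.

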#### RTSA data and police reports

As the government body mandated to register and license drivers, motor vehicles and commercial vehicle operators, RTSA maintains records of all PSVs. Any additional data required for analysis will be retrieved from RTSA. In addition, if available and timely, police reports on motor vehicle road traffic crashes for the study period will also be retrieved for analysis.

### Data analysis

At endline, full analysis will be performed using data from the full 14-month period. To assure balance between the study arms, we will compare characteristics between our two arms including insurance company provider and accident rates in the past year. Additionally, utilizing the insurance claims data, we will compare the insurance claim rate per 1000 vehicles in the 7 month period before the intervention.

For the primary outcome of the study in which will examine the change in the road traffic accident rate over the 14-month period for the intervention arm compared to the change in the road traffic accident rate over the 14-month period for the control arm, we will use a difference-in-difference analysis. To this end, we will run a difference-in-difference analysis that will be comparing the intervention and control groups using regression analysis of the following format, and adjusting the SE to account repeated measures (i.e. cluster) from the bus:$$ {\mathrm{Y}}_{\mathrm{rate}}={\upbeta}_0+{\upbeta}_{\mathrm{Sticker}}{\mathrm{X}}_1+{\upbeta}_{\mathrm{Post}}{\mathrm{X}}_2+{\upbeta}_{\mathrm{Sticker}\mathrm{Post}}{\mathrm{X}}_3+\mathrm{e} $$

For the primary outcome regression, Y is the occurrence of a road traffic crash (indicator 1, 0); X_1_ is the indicator for whether or not the bus was in the intervention arm or control arm (i.e. 0, 1); X_2_ is the indicator for the time period with a value of one indicating the seven-month post intervention period; X_3_ being the interaction indicator between the presence of the new RTSA road safety sticker and the post intervention period (difference-in-difference impact estimate). Additionally in this regression above, the β_Sticker_ estimate will provide the relative difference in the accident rate between intervention and control arm during the pre-intervention period; β_Post_ will be provide the relative change in the accident rate in the control group from pre- to post- intervention period; and, β_StickerPost_ will be the relative difference between the control and intervention group in the change in the outcome from pre to post intervention (i.e. our main estimate of effect). We will appropriately adjust for baseline imbalance between the two arms including insurance provider. To assure outcomes are more meaningful, the rates and thus betas for outcome 1 and 2 will be transformed to report per 1000 minibuses. This regression will then be replicated for the remaining study outcomes.

We will run the difference-in-difference analysis assuming intent-to-treat (ITT), in that all of those who received the assigned new RTSA road safety bus sticker (even vs. odd) will have placed the new RTSA road safety bus sticker accordingly. Though it is expected that the monitoring of RTSA will not provide perfect fidelity to the specific arms, the ITT analysis will provide a conservative estimate of effect.

Due to the nature of the study, drivers and participants cannot be blinded, however, it will be helpful to examine the effect of the new RTSA road safety bus stickers overtime to determine if Hawthorne effects, the process by which a subject of a study changes their behavior due to the knowledge that they are being surveyed and measured, reduces overtime (outcome 2). To this end the regression presented above will become a controlled interrupted time series (ITS) where each minibus will have an observation for each month for the 7-months before the intervention and 7-months after the sticker placement – a form of repeated measures analysis.

In sensitivity analysis, we will examine the difference between the study periods in our primary outcome (seven-month accident rate) controlling for baseline differences.

For outcomes with a comparison over time but not between the two study arms (outcome 4), we will run a general t-test comparison between the RTC rates before and after the intervention as well as a regression analysis controlling for any differences at baseline.

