## Discussion

Given the potential infrequency of overall RTCs (0.026 per 1000 minibuses per 6 months as reported in Kenya) and the relatively short length of the study, it is possible we will not find an impact at 7 months. There is a risk that our effect may be conservatively estimated both due to the ITT analysis but also due to potential spillover effects as passengers may go between the arms of the study; however, we feel confident there may still be a potential impact of the new RTSA road safety sticker. This is because the Kenya study similarly randomized sticker placement within the same city, thus allowing for spillover, and was able to see an impact of the sticker program. Additionally, though in the sample size calculation, we accounted for a potential improvement in the accident rate over the 14-months examined in the control group, and estimate we still anticipate some spillover thus resulting in conservative effect estimation.

Though every PSV operator is mandated by law to have valid insurance cover, the use of insurance claims data for our outcome could lead to some measurement error as not everyone files insurance claims when involved in a crash. This may be primarily prevalent in those with third party insurance who may be involved in a crash with unclaimed physical objects such as trees, walk ways, barricades etc. However, RTCs involving injuries or deaths to passengers are highly likely to be reported to insurance companies.

The outcomes, analysis, and recommendations of this evaluation are expected to inform the national scale-up of the new RTSA road safety bus stickers in PSVs by RTSA. Specifically, the results will help RTSA to understand whether the toll-free bus sticker has an impact and whether the new RTSA road safety bus stickers can improve on road safety outcomes. If only limited changes are observed, then RTSA and other national road safety stakeholders will collaborate to understand the reasons and propose further adjustments.

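### A narrowing monthly arm difference cannot show that Hawthorne effects are fading, because growing spillover or sticker loss could produce the same pattern

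*Protocol article*

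**What the plan says.** All references are to the protocol article.

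- **Purpose of the monthly analysis (Data analysis).** Because blinding is impossible, "it will be helpful to examine the effect of the new RTSA road safety bus stickers overtime to determine if Hawthorne effects" diminish. This is assigned to outcome 2. No other reason for a waning effect is named there.
- **Monthly model (Data analysis).** The difference-in-difference regression is extended to a controlled interrupted time series, with seven monthly observations per minibus before sticker placement and seven after. The parent regression has a separate term for the "relative change in the accident rate in the control group from pre- to post- intervention period".
- **Fidelity (Data analysis).** "it is expected that the monitoring of RTSA will not provide perfect fidelity to the specific arms". The plan's only conclusion from this is that the intention-to-treat estimate is conservative.
- **Spillover (Sample size and selection; Discussion).** "To account for potential spillover due to the fact that passengers will transfer between buses", the authors write, "we assumed that the control arm would have slight improvement in the accident rate over the 14-months observed". The Discussion adds that "we still anticipate some spillover thus resulting in conservative effect estimation".

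Neither spillover nor fidelity is given a time course, and neither is linked to the monthly pattern.

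**The concern.** The plan looks at one quantity, the sticker effect by month, and states one thing to be learned from its course: whether Hawthorne effects wear off. Elsewhere it expects two other processes that act on the same quantity. Passengers carry the message to control buses, and sticker display departs from allocation. If either accumulates, the arm difference shrinks without any Hawthorne fading. Habituation of passengers or drivers, which the article does not mention, would do the same.

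The explanations differ in what they mean for the scale-up decision that the Discussion and Dissemination sections describe. A difference that narrows because control buses improve suggests that the message reaches beyond the stickered buses. One that narrows because stickers come off points to upkeep. One that narrows because drivers stop reacting to being watched, or passengers stop reacting to the sticker, suggests that the effect does not last.

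**Working it through.** The article gives no figure for the monthly analysis, so there is none to reproduce. The check has two parts: whether the explanations can be told apart in principle, and how much data there is to do so. It covers minibuses only.

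**Inputs**

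- Minibuses per arm: 954 required, 1060 enrolled (Table 1). The buffer reproduces: 954 / 0.9 = 1060.
- Background rate: the Discussion prints 0.026 per 1000 minibuses in 6 months. I read it as 0.026 *per bus* in 6 months. This is an assumption. Read literally, it gives 1060 × 0.026/1000 × 7/6 ≈ 0.03 crashes per arm in seven months, and no monthly analysis would be possible.
- Assumed for illustration: the stickers halve the rate at first, and 60% of the gap is lost linearly by month 7.

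**1. Is the pattern specific to Hawthorne fading?**

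Monthly background rate: 0.026 / 6 = 0.00433 per bus, or 4.33 per 1000. Initial gap: 0.5 × 4.33 = 2.17. Gap in month k: 2.17 × (1 − 0.6 × (k − 1)/6).

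| Explanation | Control rate, month 1 to 7 | Intervention rate, month 1 to 7 | Gap, months 1 to 7 (per 1000) |
|---|---|---|---|
| Hawthorne fading (or habituation) | 4.33, flat | 2.17 to 3.47 | 2.17, 1.95, 1.73, 1.52, 1.30, 1.08, 0.87 |
| Growing sticker loss | 4.33, flat | 2.17 to 3.47 | the same |
| Growing spillover | 4.33 to 3.03 | 2.17, flat | the same |
| Constant spillover (30% of effect) | 3.68, flat | 2.17, flat | 1.52 throughout |

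- The gap is identical in the first three rows, so the gap alone cannot identify Hawthorne fading.
- The first two rows agree in both arms' series. No model of crash data separates them; information on sticker display would be needed.
- The third row differs in which arm moves, so arm-specific rates carry information that the gap does not. A falling control rate could also be a secular trend.
- The last row shows the limit of the argument: constant spillover lowers the gap but does not make it narrow.

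**2. How much data is there?**

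Crashes per arm-month before any effect: 954 × 0.00433 = 4.1, and 1060 × 0.00433 = 4.6. With the rate halved, about 2.1 to 2.3.

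For a straight line through the seven post months (Poisson variance, N = 954, sum of squared month deviations = 28), SE = √(v̄ / (28 N)), where v̄ is the mean monthly rate per bus, added over both arms for the gap. The true slope is 0.6 × 2.17 / 6 = 0.217 per 1000 per month.

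| Slope tested | v̄ per 1000 | SE per 1000 | Slope / SE | Power, two-sided 0.05 |
|---|---|---|---|---|
| Gap, under fading or sticker loss | 7.15 | 0.517 | 0.42 | 7% |
| Gap, under spillover | 5.85 | 0.468 | 0.46 | 7.5% |
| Intervention arm, under fading or sticker loss | 2.82 | 0.325 | 0.67 | 10% |
| Control arm, under spillover | 3.68 | 0.371 | 0.58 | 9% |

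A substantial narrowing would seldom be detected, and arm-specific trends can only be read descriptively.

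**The case against.** The strongest defence is that the wording is modest and the design better than the criticism suggests. The sentence offers the monthly look as helpful, outcome 2 is secondary, and the primary estimate pools the seven months. The controlled time series keeps the control arm's own course, so spread to control buses, the most consequential alternative, would appear as a falling control rate. The Discussion already names spillover and says that stakeholders would look into the reasons if only limited changes were seen.

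Much of this stands, and it rules out several stronger readings that a reader might infer:

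- *That the plan would dismiss a real benefit as an artefact.* No section says so, and there is no rule for discounting a waning effect.
- *That the plan's own assumptions imply narrowing.* They state that spillover and imperfect fidelity exist, not that they grow. Spillover from a newly placed sticker must start from nothing, so some build-up is plausible, but its length is unknown.
- *That no arm is observed without stickers.* Study design says that minibuses had not been given the toll-free sticker, and control minibuses do not receive the new one.
- *That spillover cannot be seen at all.* The model retains the series that would show it.

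The defence does not rescue the stated inference. The article ties the Hawthorne question to the sticker effect over time and does not say that the arms will be read separately. Even if they were, Hawthorne fading and sticker loss would look alike.

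**Conclusion.** Wrong as written, for a secondary analysis. Secondary outcome 2 cannot determine whether Hawthorne effects lessen, because a narrowing arm difference is equally compatible with growing spillover or declining fidelity, both of which could follow from what the plan expects, and with habituation. The primary difference-in-difference is unaffected.

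The logical point needs only that spillover or sticker loss *could* accumulate over seven months; the documents neither assert nor exclude this. The figures rest on the per-bus reading of 0.026, and the gap and power values also on the assumed 50% effect and 60% loss. They illustrate the shape and the scarcity of data and are not predictions.

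**What to change.** In the Data analysis section:

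1. Restate the purpose of outcome 2 as examining whether the difference between arms changes over the post-intervention months.
2. Say that any narrowing will be reported as compatible with Hawthorne fading or habituation, growing spillover, or declining fidelity, and will not be attributed to Hawthorne effects alone.
3. Show monthly crash rates for each arm separately and descriptively, so that a falling control rate can be told from a rising intervention rate, with the caution that a falling control rate may be a secular trend.
4. Add sticker-display results from the RTSA inspections only where these are recorded. The Intervention section describes inspections to keep stickers displayed, but Data collection procedures does not list sticker presence as a variable.

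Do not preset a rule that assigns a cause from the direction of each arm's trend. At about 4 to 5 crashes per arm-month before any effect, it would mostly sort noise.

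**Cost:** a few sentences and one display from claims data already planned. Sticker-display results could mean extra collection if inspections are not recorded, which is why that item is conditional. The plan gives up a direct claim about Hawthorne effects.
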